### Outcomes

Primary outcome parameter is the post-surgical seizure outcome after 1 year based on the Engel classification [34]. Seizure outcome will be dichotomized in seizure freedom (Engel 1A and 1B) versus seizure recurrence (Engel 1C-4). We decided to include possible auras (Engel 1B) in the seizure-free group, because it can be difficult to distinguish true auras from aura-like non-epileptic sensations. Post-surgical outcomes at 6 to 8 weeks, 6 and 12 months will be determined by means of a follow-up questionnaire completed by the patient or legal representatives. So called “running down” seizures, seizures occurring only during the first 2 weeks after surgery are not considered as seizure recurrence.

Secondary outcome parameters are:Volume of resected tissue (in cm^3^): the volume of resected tissue is determined by voxel-based volumetrics of the routine pre-surgical and post-surgical 3D whole head T1 magnetic resonance imaging (MRI) scan.Neurological deficits: neurological deficits are assessed by neurological examination and translated into the National Institutes of Health Stroke Scale (NIHSS) before surgery and before hospital discharge after surgery. The cumulated NIHSS score ranges between 0 and 42; a difference of 1 point on the NIHSS scale between the 2 tests is considered clinically relevant. In that case the NIHSS will be repeated at follow-up moments. Additionally, neurological deficits will be classified as “pre-existing” (either improved or aggravated) or as “new” (either anticipated or unexpected).Duration of surgery: post-hoc analysis of duration of surgery (start-stop time neurosurgeon, in minutes) and ioECoG recording time (in minutes).Surgical complications: accounts are kept of the number of (post-) operative complications, such as bleeding, infection, unexpected or aggravated neurological deficits. These events will also be reported as (serious) adverse events ((S)AE).Cognition: comparison of results from pre-operative and 12-month post-operative neuropsychological evaluation. This routine neuropsychological evaluation includes testing of IQ, working memory and processing speed. All tests performed are chosen according to the age of the patient, but report on the same domains. Per domain individual patients’ results will be dichotomized into negative, no, or positive change compared to pre-surgical baseline.Quality of life (QoL): QoL will be determined pre-operatively, and post-operatively after 6 to 8 weeks, and 6 and 12 months using a visual analog scale (VAS) on overall self-perceived quality of life, or by the parents in case of children < 12 years of age.

Data collection, management and storage is done in open source clinical trial software OpenClinica (OpenClinica, LLC, Waltham, MA, USA; www.openclinica.com), managed by the IT division of the Neurology and Neurosurgery Department of the UMC Utrecht. Figure 1 shows the timeline of the study procedures.

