**Discussion:**

This trial provides a transition from observational research towards clinical interventions using HFOs. We address methodological difficulties in designing this trial. We expect that the use of HFOs as a biomarker for tailoring will increase the success rate of epilepsy surgery while reducing resection volume. This may reduce neurological deficits and yield a better quality of life. Future technical developments, such as validated automatic online HFO identification, could, together with the attained clinical knowledge, lead to a new objective tailoring approach in epilepsy surgery.

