### Blinding

Blinding of the treating physicians and neurosurgeons for treatment allocation is not feasible because of the character of the intervention. Therefore, this is a single-blinded trial as patients will be blinded for the treatment allocation to avoid bias of the follow-up results. To guaranty the blinding of the patient, the outpatient physicians, neurologist and psychologist involved in the follow-up procedures are blinded for the ioECoG report during the entire period of follow-up. After study completion or termination patients who wish so will be de-blinded.

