### Statistical methods

The primary “intention-to-treat” analyses at study completion are based on the difference between the treatment arms with respect to surgical outcome after 12 months. The primary outcome is a categorical outcome, seizure freedom versus seizure recurrence. Risk ratios (RR) and risk difference with 95 % confidence interval will be calculated (*X*^2^- test, 1-sided). Secondary outcomes are the amount of tissue resected, neurological deficits, duration of surgery, complications, cognition and quality of life. For the secondary outcome parameters consisting of continuous variables, a *T*-test with 95 % confidence interval is calculated and tested (1-sided). For the secondary outcome parameters consisting of categorical variables, the RR and risk difference with a 95 % confidence interval are calculated and tested using a Chi-square test (1-sided). Logistic regression analysis will be performed: 1) to adjust for the stratification factors, by including site and epilepsy type as variables in analysis, and 2) to investigate if there are relations between seizure outcome and subject variables, such as age, gender, and pathology, or with experimental variables, such as the operating surgeon and the amount of anesthesia received. Note that we are not going to use a mixed model to adjust for site, as we consider two sites too small a sample to be representative for other sites. Regression analysis is also performed between seizure outcome and the secondary outcome parameters.

In the logistic regression analysis we will, after screening of the number of missing data, perform multiple imputation. For the primary and secondary endpoint no imputation will be performed. Statistical analysis will be performed in SPSS version 21 (SPSS Inc., Chicago, IL, USA) or higher and/or R version 3.1 or higher.

The number of eligible patients withholding consent will be registered, and demographic information will be collected anonymously for post-hoc explorative analysis to understand potential bias in study outcomes.

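### Resected volume is compared in raw cm³ by an unadjusted t-test in a very mixed population; the test is valid but gives away precision that baseline adjustment would recover

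*Protocol article*

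**What the plan says.** In the protocol article, Outcomes, resected volume is the first secondary outcome listed. It is given in cm³, and "the volume of resected tissue is determined by voxel-based volumetrics of the routine pre-surgical and post-surgical 3D whole head T1" MRI scan. It is not expressed relative to brain, lobe, lesion or planned volume.

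Statistical methods fixes the comparison. The sentence that opens "For the secondary outcome parameters consisting of continuous variables" assigns a t-test with a 95 % confidence interval, 1-sided, and names no covariate. Adjustment appears only under logistic regression, whose first purpose is "to adjust for the stratification factors, by including site and epilepsy type as variables in analysis". One further sentence involves the secondary outcomes: "Regression analysis is also performed between seizure outcome and the secondary outcome parameters". That relates volume to seizure outcome; it does not compare volume between arms.

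The population is mixed. Considerations includes children with no lower age limit. Participants describes one site with 75 % of patients under 18 and one that operates on adults only. Randomization stratifies by site (described as an indirect stratification for age) and by temporal versus extra-temporal epilepsy.

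The Abstract expects that HFO tailoring "will increase the success rate of epilepsy surgery while reducing resection volume".

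**The concern.** Brain size, and temporal versus extra-temporal site of resection, can plausibly move resected volume a good deal whatever marker guides the tailoring. The design treats site and epilepsy type as important enough to stratify on, yet the volume comparison ignores both. A t-test that omits the strata does not credit the balance they achieve in its standard error. A comparison of arithmetic means in cm³ is also sensitive to a few large resections if volumes are right-skewed.

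At stake is the trial's ability to show a smaller resection at equal seizure outcome. In a non-inferiority trial that would be part of the case for HFOs, and the sample size was set without reference to it.

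**Working it through.** **Inputs from the article.** 39 per group, 1-sided 5 %, 80 % power, rates 65 % and 80 %, non-inferiority limit 10 % (Sample size); 1-sided t-test for volume (Statistical methods).

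**Inputs assumed, because the article gives none.** Lognormal volumes; SD of log volume s = 0.6, 0.8 or 1.0 (coefficient of variation √(exp(s²) − 1) = 0.66, 0.95, 1.31); true ratio of volumes 0.7, a 30 % reduction; share of variance explained by baseline covariates, R² = 0.2 to 0.5.

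**Step 1: the plan's own figure.** n = (0.65 × 0.35 + 0.80 × 0.20) × (1.645 + 0.842)² / (0.15 + 0.10)² = 38.3, so 39 per group. The stated number reproduces, but it concerns the binary primary outcome only.

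**Step 2: what 39 per group can detect for volume.** The difference detectable with 80 % power is (1.645 + 0.842) × √(2/39) = 0.56 SD unadjusted. With adjustment it is multiplied by √(1 − R²), and the equivalent unadjusted group size is 39/(1 − R²).

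| R² | Detectable difference | Equivalent n per arm |
|---|---|---|
| 0 | 0.56 SD | 39 |
| 0.2 | 0.50 SD | 49 |
| 0.3 | 0.47 SD | 56 |
| 0.5 | 0.40 SD | 78 |

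The share of attainable precision (1/variance) lost by not adjusting is R² itself.

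**Step 3: power for a 30 % reduction, 39 per arm, 1-sided 5 %** (simulation).

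| Analysis | s = 0.6 | s = 0.8 | s = 1.0 |
|---|---|---|---|
| t-test on raw cm³ (as planned) | 78 % | 53 % | 36 % |
| t-test on log volume | 84 % | 62 % | 47 % |
| Log-scale ANCOVA, R² = 0.2 | 90 % | 71 % | 55 % |
| Log-scale ANCOVA, R² = 0.5 | 98 % | 86 % | 70 % |

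The log-scale rows can be checked by hand with power ≈ Φ(|ln 0.7| / (s √(1 − R²) √(2/39)) − 1.645). For s = 0.8 and R² = 0.2 this is 0.357 / (0.8 × 0.894 × 0.226) − 1.645 = 0.56, and Φ(0.56) = 0.71. A fresh run of 20,000 trials per setting agreed with every cell to within about one point.

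**Step 4: validity.** With no true difference, the raw t-test rejected in about 5 % of simulated trials at each s. Skewness of this degree does not spoil the error rate at 39 per arm.

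**The case against.** The strongest reply is that nothing here is an error. The t-test is valid after randomisation, a mean difference in cm³ is a legitimate and readable estimand, and transformations and covariates for secondary outcomes are often settled in an analysis plan, which is not shown. The first two points stand: this is a matter of efficiency. The third stands only in part, because the article does not leave the test open. It names one, and its only adjustment for the strata is in a model unsuited to volume.

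Several stronger readings are tempting, and the documents do not support them:

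- *Volume is the main expected benefit.* The Background puts seizure freedom first and lists a smaller resection among other possible benefits. It is one of several secondary objectives.
- *Most of the precision is wasted.* That needs R² above 0.5, and nothing in the article allows R² to be estimated.
- *A real reduction would probably be missed.* Under the planned 1-sided test a 30 % reduction is detected with 78 % power at s = 0.6, and 53 % at s = 0.8 is close to even odds. Only towards s = 1.0 is it more likely missed than found. At s = 0.4 or 0.5, raw power is 98 % or 90 %. The exclusion of hemispherectomies and disconnections (Participants) also removes some extreme procedures.
- *A chance imbalance could create a spurious effect.* That is ordinary type I error, which stays near 5 %, and stratification limits imbalance in site and epilepsy type.
- *Lesion size is already available and sets the resection.* Interventions ties the resection to lesion size only in the fallback case, where neither HFOs nor ictiform spike patterns are found. Lesion volume would be a new measurement.
- *The volumetry is unblinded.* The Blinding section says that "the outpatient physicians, neurologist and psychologist involved in the follow-up procedures are blinded for the ioECoG report", in order to protect patient blinding. That it does not mention an imaging reader is detail a condensed article may omit.

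**Conclusion.** The point holds as an efficiency improvement. The stated analysis of resected volume is valid but unadjusted, in a population whose heterogeneity the design itself recognises. Under the assumptions above, log-scale ANCOVA raises power for a 30 % reduction by 12 to 20 percentage points at s = 0.6 (78 % to 90–98 %), 18 to 33 at s = 0.8 (53 % to 71–86 %) and 19 to 34 at s = 1.0 (36 % to 55–70 %). The log scale alone accounts for 6, 9 and 11 of these points (84 − 78, 62 − 53, 47 − 36), and the rest depends on R².

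The direction is the same in every setting tried. The size is conditional on the assumed lognormal shape, SD and R². The primary outcome and its sample size are not affected.

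**What to change.** In Statistical methods, take resected volume out of the general t-test rule and specify a linear model (ANCOVA) with arm, site, epilepsy type and age. Fix this before volumes are compared by arm. Preferably model log volume, report the ratio of geometric means with its confidence interval, and give the raw cm³ difference descriptively.

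Add whole-brain volume from the pre-surgical T1 scan already used for the volumetry. Lesion volume is optional, with a rule for patients who have no lesion.

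Cost: site and epilepsy type are known at randomisation and age is already listed for the regression analyses, so these three need wording only. Whole-brain volume needs a little segmentation work. No extra patients, visits or scans are required. On the log scale the estimand changes from a difference in cm³ to a ratio, which should be stated openly. If a cm³ estimand is preferred, the same covariates can be used on the raw scale; that keeps the gain from adjustment and forgoes the gain from the log scale.

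### The stated t-test for quality of life takes one value per patient from four scheduled assessments, names no visit, and by itself uses neither the baseline score nor the other visits

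*Protocol article*

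**What the plan says.** The Outcomes section schedules four QoL assessments per patient, one before surgery and three after: "QoL will be determined pre-operatively, and post-operatively after 6 to 8 weeks, and 6 and 12 months using a visual analog scale".

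Statistical methods includes QoL in its list: "Secondary outcomes are the amount of tissue resected, neurological deficits, duration of surgery, complications, cognition and quality of life". The analysis rule is generic: "For the secondary outcome parameters consisting of continuous variables, a *T*-test with 95 % confidence interval is calculated and tested (1-sided"). On missing values the section says: "For the primary and secondary endpoint no imputation will be performed". Multiple imputation is kept for another purpose: "In the logistic regression analysis we will, after screening of the number of missing data, perform multiple imputation".

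The section also comments on mixed models: "Note that we are not going to use a mixed model to adjust for site". The reason given is that there are only two sites, so the remark does not concern repeated measurements on the same patient.

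Two other outcomes do have a fixed time point. The primary analysis is "based on the difference between the treatment arms with respect to surgical outcome after 12 months", and Outcomes defines cognition as a pre-operative to 12-month comparison. No visit, change score or summary measure is named for QoL.

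**The concern.** A two-sample t-test needs a single number per patient, and the VAS yields up to four. The stated method therefore does not match the data collected. It leaves open which number is compared, and it has no place for the baseline score or the within-patient correlation between visits. It also omits the two stratification factors, site and epilepsy type, which the article adjusts for only in the logistic regression.

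QoL matters here because the Abstract, Background and Expected benefit sections all present it as a hoped-for gain from HFO-guided tailoring. The sample size was set for seizure outcome, so a QoL comparison has to make the most of 39 patients per arm. An unnamed visit also leaves room to choose the time point after the data are seen.

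**Working it through.** **Inputs from the protocol article (Sample size):** 39 per arm; one-sided 5 %; 80 % power; success 65 % against 80 %; non-inferiority limit 10 %.

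**Assumption:** the article gives no SD, correlation or missing rate for the VAS. Results are therefore in SD units, with one common correlation ρ between all assessments, taken as 0.5 (range 0.3 to 0.7).

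**Step 1. The plan's own figure.** With unpooled variance, n = (1.645 + 0.842)² × (0.65×0.35 + 0.80×0.20) / (0.10 + 0.15)² = 6.19 × 0.3875 / 0.0625 = 38.3, so 39 per arm and 78 in total. The stated figure reproduces. It is not a power statement for QoL.

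**Step 2. Detectable QoL difference.** The formula is (1.645 + 0.842) × √(2v/39), which equals 0.563 × √v SD, where v is the variance relative to a single-visit t-test:

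- single-visit t-test: v = 1
- 12-month value adjusted for baseline: v = 1 − ρ²
- mean of the 6- and 12-month values adjusted for baseline: v = (1 + ρ)/2 − ρ²

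| ρ | t-test, one visit | 12 months, baseline-adjusted | 6- and 12-month mean, baseline-adjusted |
|---|---|---|---|
| 0.3 | 0.56 | v = 0.91, 0.54 | v = 0.56, 0.42 |
| 0.5 | 0.56 | v = 0.75, 0.49 | v = 0.50, 0.40 |
| 0.7 | 0.56 | v = 0.51, 0.40 | v = 0.36, 0.34 |

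**Step 3. Source of the gain.** With complete data, the 12-month contrast from a repeated-measures model has essentially the variance of a baseline-adjusted 12-month analysis. The step from 0.56 to 0.49 SD is thus mainly baseline adjustment. Earlier post-operative visits add to the 12-month contrast only where 12-month values are missing. The further step to 0.40 SD belongs to the averaged contrast alone. At ρ = 0.5 its variance is a third below that of the adjusted 12-month value (0.50 against 0.75).

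**Step 4. Same comparison as power.** For an assumed true difference of 0.5 SD, the single-visit t-test has 71 % power. The baseline-adjusted 12-month analysis has 75 %, 82 % and 93 % at ρ = 0.3, 0.5 and 0.7.

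**Step 5. Missing visits.** If 5, 10 or 15 % of values were missing at the tested visit (assumed rates), a t-test there would keep about 37, 35 or 33 patients per arm and detect about 0.58, 0.59 or 0.61 SD.

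**The case against.** The strongest reply is that this is an unpowered secondary outcome in a condensed article. A full protocol or analysis plan, not at hand, may name the visit, and a t-test at a named visit is simple and defensible. That is fair as far as the missing visit goes, and it keeps the point small. It does not fully answer it: the article does fix the method, down to sidedness and the imputation rule, and that method does not suit data measured four times.

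A second reply is that a t-test can be run on a change score or on a per-patient mean of the visits. It can, though the article names neither. A change score has relative variance 2 − 2ρ. That is 1.4, 1.0 and 0.6 at ρ = 0.3, 0.5 and 0.7, so it is never better than baseline adjustment in this range and gains nothing at 0.5.

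Three stronger readings are tempting, and the article does not support them:

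- **That patients who miss one visit are dropped.** No complete-case rule is stated. Such a patient would be absent only from a test at that visit. Declining imputation does not rule out a likelihood-based model that uses the values present. Sample size also expects little loss to follow-up and ties the questionnaires to routine visits.
- **That QoL will be tested three times.** Testing each visit at one-sided 5 % without adjustment would raise the chance of at least one false positive to about 13 %, 12 % or 10 % at ρ = 0.3, 0.5 or 0.7. Nothing says this will be done.
- **That the t-test can find only large differences.** No VAS SD or clinically important difference is given by which to judge 0.56 SD.

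**Conclusion.** The point holds as a modest improvement to a secondary analysis. As stated, the QoL test has no named visit and makes no use of the baseline VAS or the repeated structure.

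The benefit for the 12-month QoL result is a fall in the detectable difference from 0.56 to about 0.49 SD (0.54 to 0.40). A reader might credit the full drop to 0.40 SD to that result. It applies only to the averaged 6- and 12-month contrast, and only if the effect is similar at both visits.

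All these figures rest on the assumed common correlation of 0.3 to 0.7, equal variances across visits and 39 patients per arm with complete data. The seizure-freedom comparison is not touched.

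**What to change.** For QoL, replace the t-test by one repeated-measures linear model for the post-operative VAS:

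- Fixed effects: arm, visit, arm-by-visit, baseline VAS, site and epilepsy type, with correlated values within patient. Entering site as a fixed effect is consistent with the article's refusal of a mixed model for site.
- Patients: everyone with at least one post-operative value, with no imputation of missing visits.
- QoL result: the arm contrast at 12 months.
- Supporting estimate: the average of the 6- and 12-month contrasts.

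The cost is one sentence in Statistical methods, added before the data are analysed. SPSS and R, both already named, can fit the model, and no further data are needed. The small downside is that the averaged contrast is a slightly different quantity from the 12-month value, so the two should be labelled separately.

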**Fig. 1 Fig1:**
[figure not shown]
Timeline of the study procedures. On the day prior to surgery, the patient signs the informed consent form and subsequently the baseline questionnaire and neurological examination (by means of National Institutes of Health Stroke Scale (NIHSS)) are completed and the patient is enrolled in the study by randomization. Note that the follow-up questionnaire collects information about (preliminary) outcome, anti-epileptic drug use, quality of life and occurrence of (serious) adverse events. Additional information is collected from routine clinical tests that are performed during the pre-surgical and post-surgical period

**Fig. 2 Fig2:**
[figure not shown]
Logotype “The HFO Trial”

### Sample size

The sample size calculation is based on a success rate of surgery (defined as Engel 1A or 1B at 1 year) in the control group (tailoring based on spikes) of 65 %, and the expected success in the experimental group (HFOs) of 80 %. The resulting margin is 15 %. Using a 1-sided 95 % confidence interval and a non-inferiority limit of 10 %, to acquire an 80 % power we need 39 patients per group. This results in a total of 78 patients. We anticipate that 80 % of the eligible patients will participate in the study.

We expect the potential loss-to-follow-up after the initial intervention to be low. Routine clinical visits to the neurosurgeon and neurologist are scheduled after surgery at 6 to 8 weeks, 6 months and 12 months. Our FU questionnaires coincide with these visits. Inclusions will proceed until the target sample size is achieved to address loss to follow-up. Loss to follow-up can be expected from; 1) withdrawal by the subject from the study during follow-up before the first preliminary outcome determination at 6–8 weeks, and 2) withdrawal from the study during the surgery by the surgeon or dedicated team due to urgent medical or technical issues.

Subjects are replaced if they withdraw from the study during follow-up before the first preliminary outcome determination at 6–8 weeks. Subjects who are withdrawn from the study during the surgery by the surgeon or dedicated team due to urgent medical or technical issues are also replaced.

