### Interventions

Participating patients who will undergo ioECoG-tailored surgery will be randomized into an HFO-guided (arm 1) or standard epileptiform spikes-guided (arm 2) resection.

The ioECoG is routinely recorded at a sampling frequency of 2048 Hz using clinical electroencephalogram (EEG) software. A dedicated HFO team, including two experienced HFO observers, will perform the analysis during surgery when the patient has been allocated to the HFO arm. The HFO reviewers need to achieve consensus about the HFOs and distinguish them from artifacts. This team will, together with the clinical neurophysiologist in charge, advise the neurosurgeon on the extent of the tissue to be resected. HFO analysis is performed visually and off-line using Stellate Harmonie Reviewer (v7.0, Montreal, QC, Canada), as this is currently the only clinical EEG software that provides HFO visualization and marking. A split screen modus will be used to simultaneously visualize ripples (settings: finite impulse response (FIR) filter > 80 Hz, gain 5 μV/mm) and fast ripples (settings: FIR filter > 250 Hz, gain 1 μV/mm) at an elongated time interval of 0.4 s/page, according to the settings described in other studies [15, 18, 21, 22]. Based on pilot data, we expect that the visual analysis of HFOs will require 50 % more time compared to the visual analysis of epileptogenic spikes, which usually takes 3 to 5 minutes per recording. This is an intention-to-treat study. HFOs in eloquent regions will not be resected, similar to standard tailoring practice based on spikes. In absence of HFOs, ictiform spike patterns (for definition see introduction) [11] will always be resected, irrespective of treatment allocation. If no HFOs or ictiform spikes are found a planned resection is performed according to size and location of epileptogenic structural lesion(s), similar to standard clinical practice when no spikes could be identified.

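### Patients withdrawn in theatre or before 6–8 weeks are replaced after randomisation and counted as lost, which conflicts with the stated intention-to-treat analysis

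*Protocol article*

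**What the plan says.** - **Timing.** The Randomization section places consent on the day before surgery, with allocation following consent. The Fig. 1 legend agrees: on that day "the patient is enrolled in the study by randomization". Any withdrawal in theatre is therefore after allocation.
- **Replacement in theatre.** Sample size: patients "withdrawn from the study during the surgery by the surgeon or dedicated team due to urgent medical or technical issues are also replaced".
- **Replacement in early follow-up.** Sample size: "Subjects are replaced if they withdraw from the study during follow-up before the first preliminary outcome determination", that is, at 6–8 weeks.
- **Status of these patients.** The same section lists both groups as the expected sources of loss to follow-up and keeps recruiting until the target number is reached.
- **Analysis.** Interventions: "This is an intention-to-treat study". Statistical methods gives the primary analysis the same label and rules out imputation for the primary and secondary endpoints.
- **Who knows the allocation.** Blinding: surgeons are not blinded; patients are. Interventions: the dedicated HFO team "will perform the analysis during surgery when the patient has been allocated to the HFO arm".
- **Feasibility.** Trial design makes feasibility of HFO tailoring part of the primary objective. Considerations calls assessing it the most important aspect of the study.

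**The concern.** Intention-to-treat means that each randomised patient is compared in the arm to which he or she was allocated. A patient who has left the study, is counted as lost, has no imputed outcome and has been replaced contributes nothing to the primary comparison. The two statements cannot both be followed.

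For withdrawals in theatre the loss may also differ between arms. The HFO analysis needs separate off-line software, two observers in consensus and separation of HFOs from artifact. A breakdown in that chain can occur only in the HFO arm. The surgeon, who may withdraw a patient, knows the allocation. If withdrawn patients have a poorer prognosis, their replacement raises the observed HFO success rate, and in a non-inferiority trial that favours the claim. Whatever its effect on the rate, a patient in whom HFO tailoring had to be abandoned is evidence on feasibility, and substituting that patient takes the case out of the comparison.

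Early withdrawal is different. The blinded patient makes the decision, so it has the intention-to-treat conflict but no route through unblinded staff.

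**Working it through.** **1. The plan's own sample size.** Inputs from Sample size: success "in the control group (tailoring based on spikes) of 65" %, and "the expected success in the experimental group (HFOs) of 80" %. "Using a 1-sided 95 % confidence interval and a non-inferiority limit of 10" %, so one-sided alpha is 0.05 and the margin 0.10. Power is 80 %.

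n per arm = [0.65×0.35 + 0.80×0.20] × (1.645 + 0.842)² / (0.15 + 0.10)² = 0.3875 × 6.183 / 0.0625 = 38.3, rounded up to 39.

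This reproduces the stated 39 per arm and 78 in total. The arithmetic is sound. The issue is which 78 patients are counted, because 39 per arm is a number reached after replacement.

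**2. Effect of replacement on the observed rate.** Let p be the true success rate of all patients randomised to HFO, f the share removed and replaced, and q the success rate that the removed patients would have had. The rate in those analysed is

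r = (p − f·q) / (1 − f).

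If q = p, then r = p and there is no bias. If q < p, r is too high. If q > p, r is too low.

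**3. Effect on the false non-inferiority rate.** Take the boundary case: spikes 0.65, HFO 0.55, 39 per arm, removals in the HFO arm only.

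SE = √[(0.65×0.35 + r(1 − r)) / 39]

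P(claim) = Φ[(r − 0.65 + 0.10)/SE − 1.645]

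The document gives no f and no q, only an expectation that loss will be low. Both are assumptions here, shown as ranges.

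| Share removed, f | q = 0.55 (no link to prognosis) | q = 0.40 | q = 0.30 |
|---|---|---|---|
| 2.5 % (1 of 40) | 5.0 % | r = 0.554, 5.4 % | r = 0.556, 5.6 % |
| 5 % | 5.0 % | r = 0.558, 5.8 % | r = 0.563, 6.4 % |
| 10 % | 5.0 % | r = 0.567, 6.8 % | r = 0.578, 8.2 % |

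Worked cell (f = 0.10, q = 0.30): r = (0.55 − 0.03)/0.90 = 0.578; SE = √[(0.2275 + 0.2440)/39] = 0.110; 0.0278/0.110 = 0.253; Φ(0.253 − 1.645) = 0.082.

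As an extreme, if every removed patient would have failed (q = 0), one removal gives about 6.5 % and two give about 8.3 %.

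**4. The opposite effect, if abandoned cases are kept.** Suppose HFO tailoring itself has 55 % success, and in 10 % of the arm it is abandoned, with control-like success of 65 %. The arm rate is 0.9×0.55 + 0.1×0.65 = 0.56, and P(claim) is about 6.0 %. Retention therefore does not fully protect against a false claim about HFO tailoring itself.

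**The case against.** The replacement rules stand under Sample size and can be read as recruitment rules only. Replacement does not break intention-to-treat if the replaced patients are still followed and analysed as allocated, and analysis sets are usually defined in a full protocol or SAP that is not shown here. That is fair as far as it goes. But this article does more than top up recruitment: it describes these patients as withdrawn from the study, counts them as lost and bars imputation. Nothing in it brings them back. The conflict is in what is stated, not in what is left out.

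Four stronger readings are tempting, and the documents do not support them:

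- **That replacement makes the HFO arm look better.** This holds only if removal is linked to poor prognosis. A software or equipment failure has no documented link, and without one the bias is zero.
- **That staff can remove patients at will.** Withdrawal in theatre is limited to urgent medical or technical problems. The phrase is undefined but restrictive. Absent HFOs and HFOs in eloquent cortex are handled within the allocated strategy (Interventions), and the surgeon can withdraw patients in either arm.
- **That the HFO team attends only HFO-arm surgery.** The text gives the team its task in that arm but does not exclude it from control surgery.
- **That failures are concealed.** Non-feasibility is a ground on which the Data Monitoring Committee can advise stopping (Interim analysis), and nothing says that withdrawals go unreported.

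**Conclusion.** The concern holds as a conflict within the protocol article. Two groups of randomised patients are replaced and treated as lost, with no imputation, in an analysis labelled intention-to-treat. This decides who enters the primary non-inferiority comparison, so it should be corrected. The possibility of arm-dependent removal applies only to withdrawals in theatre.

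Confidence is high on the conflict and low on any bias. Under the assumptions in the table, the false non-inferiority rate runs from 5.0 % (no link to prognosis) to 8.2 % (10 % of the HFO arm removed, 30 % success among them). With the low loss that the protocol expects, the effect would be nearer the 5.4–5.6 % of a single removal. A reader might infer that the trial is biased towards HFOs; the document establishes neither the direction nor the size. The case for correction rests on the conflict and on the feasibility information at stake, not on the 10 % scenario.

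**What to change.** 1. Drop replacement as substitution. State that every randomised patient stays in the allocated arm for the primary intention-to-treat analysis, including those in whom the allocated tailoring was abandoned.
2. Follow these patients to 12 months through the routine visits, where consent allows.
3. Treat any further inclusions as additional to the patients already randomised. If attrition is to be planned for, inflate the total: 78/0.95 = 82.1, so 83 at an assumed 5 %, or 78/0.90 = 86.7, so 87 at 10 %.
4. Report withdrawals in theatre by arm, with reasons, as a feasibility result.
5. Add a per-protocol companion analysis and a sensitivity analysis for missing 12-month outcomes.

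The clinical grounds for withdrawal in theatre remain with the sponsor.

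**Cost.** Mainly wording, since the 12-month visit is routine care. Slightly more than 78 patients may be randomised. Retained abandoned cases dilute the contrast, which can itself favour non-inferiority (about 6.0 % in the example above); the per-protocol companion is there for that reason.
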